### Inclusion criteria

Diagnostic criteria for COVID-19 are based on the Protocol for the Diagnosis and Treatment of Novel Coronavirus Disease 2019 (9th edition) released by the NHC of the People's Republic of China (General Office Of The National Health And Health Commission, 2022) and include individuals who qualified for eligibility meeting the following criteria: 1) clinically confirmed patients of COVID-19 according to the Protocol for Diagnosis and Treatment of Novel Coronavirus Pneumonia (9th edition) with laboratory confirmed SARS-CoV-2 infection as determined by RT-PCR; 2) patients judged to have mild or moderate COVID-19. (Patients with mild COVID-19 usually present with mild clinical symptoms, without radiological manifestations of pneumonia, whereas patients with moderate COVID-19 patients have a fever and respiratory symptoms, as well as radiological features of pneumonia); 3) presence of one or more symptoms of fever, cough, sore throat, and fatigue when entering the group; 4) the time of admission is not more than 24 hours; 5) patients of either sex who are 18 years or older, and 6) providing written informed consent before enrolling in the trial.

### Exclusion criteria

Patients are ineligible for the study if they meet any of the following criteria: 1) show the early warning indicators of severe or critical condition; 2) use similar Chinese patent drugs before enrollment; 3) immunodeficiency diseases or use of immunosuppressants or glucocorticoids within the last 3 months; 4) pregnancy, lactation, or intention to become pregnant; 5) allergic constitution (referring to those allergic to more than two types of drugs or foods or the known ingredients of the investigational medications); 6) mental illness, or without self-knowledge ability, and 7) other conditions judged by the investigators.

### Withdrawal criteria and termination criteria

First, the investigator's decision to withdraw the patient is based on the following principles: 1) during the clinical trial, the patients develop diseases that are not suitable for further study; 2) patients with adverse events or serious adverse events are not suitable to continue the study, and 3) other conditions that the researchers believe will harm the health of the patients by continuing the study.

Second, patients can and should withdraw if they are unwilling to continue with the clinical trial. According to the provisions of the informed consent form, participants can withdraw at any time during the study. If patients have not explicitly proposed to withdraw but no longer accept medication and testing, as well as loss to follow-up, are regarded as 'withdrawal'. The reasons for withdrawal should be known and recorded as precisely as possible. Examples include consciously being unable to tolerate adverse events, inability to continue clinical research due to other reasons, or loss to follow-up without explaining the reasons. In electronic case report forms (eCRFs), the reasons for dropout will be recorded and the data analysis will include their last record.

Third, when reviewing the data prior to statistical analysis, it is up to the principal investigator (PI) and statisticians to judge whether an individual case is excluded. If one of the following events occurs, the two sides should consider whether the patient should be excluded based on the study's progress and the reasons for withdrawal and provide a detailed explanation: 1) After randomization, individuals not meeting the selection criteria or meeting the exclusion criteria of the research proposal are found; 2) The failure to take at least one dose of trial medication and the lack of any data post-randomization.

Fourth, the conditions for stopping early are as follows: 1) if a high incidence of serious adverse events is found during the research, the study should be suspended in time; 2) if during the research, significant mistakes are found in the research proposal or there are serious deviations in its implementation, making it difficult to evaluate the efficacy of drugs, the research should be stopped; 3) the ethics committee requests to suspend or terminate the research; 4) the administrative department cancels the research.

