### Interventions measures

Patients in the SHHS group will receive SHHS granules (10 g per bag), two bags at a time, three times a day, to be swallowed with warm water. The administration of LHQW granules (10 g per bag) will be the same as the SHHS group. The medication course was 7 days (the medication could be stopped in advance if the discharge standard was reached). It will be forbidden to receive other TCM for COVID-19 treatment during the treatment period, including TCM decoctions, granules, or proprietary Chinese medicine. The types, dosage, and cumulative time (including the start and end dates) of the combined therapy drugs should be recorded during the observation period. The intervention will be stopped if there are any severe adverse effects or withdrawal.

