### Blinding

The SHHS used in this study is provided by Jiangsu Kanion Pharmaceutical Co. Ltd. (Lianyungang City, Jiangsu Province, China). LianHuaQingWen granules were purchased from Shijiazhuang Yiling Pharmaceutical Co., Ltd. (Shijiazhuang, China). All medications are administered under good manufacturing practices. Even though the trial is open-label, the research assistants who allocate patients to groups will be unaware of their treatment allocation before grouping. Also, assessors and statisticians will be blinded to the group assignment when assessing the efficacy and analyzing the data. Before the analysis and evaluation, all samples and data are anonymized.

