### Definition of analysis sets

(1) Full analysis set (FAS): All participants randomly assigned to the group, use the medicine at least once, and have at least one visit will be analyzed using intention-to-treat analysis of the entire dataset.(2) Per protocol set (PPS): This includes all participants who comply with the research protocol, which have no missing data on important baseline variables and primary outcome. Major violations on concomitant medicine and extremely lower compliance will be considered to be excluded from PPS.(3) Safety set (SS): All randomized participants could be included in SS if they have used at least one dose of drugs and have completed at least a one-time safety assessment. Impution will not be conducted for safety outcomes in SS.

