### Imputation of missing data

Missing values of the primary and secondary outcomes will be carried forward from the latest observation data to the final results (LOCF method).

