### Analysis of primary outcome

The primary analysis will be conducted on the FAS and PPS, which is the rate of self-reported clinical symptoms, including fever, fatigue, and coughing recovery. The percentage of patients whose clinical symptoms disappeared on the seventh day will be summarized. CMH-Chisquare test will be applied to compare rates between groups and Clopper-Pearson method will be used to calculate the 95%CI for rate difference (Table 3).

**Table 3 T3:** Analysis of the primary outcome.

	Full analysis set				Per Protocol set			
Variables	SHHS group (n=xx)	LHQW Group (n=xx)	Rate difference 95%CI	*P-Value*	SHHS group (n=xx)	LHQW Group (n=xx)	Rate difference 95%CI	*P-Value*
Rate of clinical symptom recovery at days 7 (n,%)^b^	xx (xx%)	xx (xx%)	xx%(xx% to xx%)	.xx	xx (xx%)	xx (xx%)	xx%(xx% to xx%)	.xx

b Number, percentage.

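### Safety-related withdrawal removes patients from the study rather than only from study drug, so last-observation imputation may replace day-7 outcomes that could still be collected

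*Protocol article*

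**What the plan says.** All references are to the protocol article.

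- **Withdrawal criteria and termination criteria, first paragraph.** The investigator's "decision to withdraw the patient is based on the following principles": a disease arising during the trial that makes further participation unsuitable, adverse events ("patients with adverse events or serious adverse events are not suitable to continue the study"), and other conditions in which continuing would harm the patient. What the patient leaves is the study, not only the drug.
- **Same section, second paragraph.** This covers patients who leave by choice, refuse medication and testing, or are lost. It ends by saying that "the reasons for dropout will be recorded and the data analysis will include their last record".
- **Interventions measures.** "The intervention will be stopped if there are any severe adverse effects or withdrawal". Assessment afterwards is not mentioned.
- **Table 1.** Symptoms, clinical assessment, concomitant drugs and adverse events are scheduled daily to day 8; drug administration ends on day 7.
- **Imputation of missing data.** "Missing values of the primary and secondary outcomes will be carried forward from the latest observation data to the final results". No reason for missingness is treated differently.
- **Analysis of primary outcome.** "The primary analysis will be conducted on the FAS and PPS". Definition of analysis sets describes the full analysis set (FAS) analysis as intention-to-treat.
- **Blinding.** The trial is open-label; "assessors and statisticians will be blinded to the group assignment when assessing the efficacy and analyzing the data". The investigator who decides on withdrawal is not named there.

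**The concern.** Stopping study drug and leaving the study are different events. A patient who stops drug for an adverse event usually remains assessable, and here day 7 is at most six days after the first dose. If withdrawal ends assessment, the day-7 result goes missing because of how the patient was doing, and LOCF puts an earlier status in its place.

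In the FAS three kinds of patient can be misclassified: those withdrawn while worsening but before meeting severe criteria; those symptom-free at the last record but not on day 7; and those symptomatic at the last record who recover by day 7. A patient already classed as severe keeps that status.

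The investigator deciding on withdrawal may know the arm. If withdrawal, or the gap between last-record and day-7 status, differs by arm, the non-inferiority comparison can be biased either way. A later analysis plan can change the imputation method but cannot recover data that were never collected.

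**Working it through.** **1. The plan's own figure.** Inputs from Sample size: LHQW 87%, SHHS 90%, margin 10 points, one-sided 0.025, power 80%. With unpooled variance,

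n = (1.96 + 0.8416)² × (0.87×0.13 + 0.90×0.10) / 0.13² = 94.3 per arm.

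The plan states 94, so the figure reproduces. With 20% dropout, 94/0.8 rounds up to 118 per arm; the plan enrols 120.

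**2. Formula for the illustrations.** Normal approximation, 120 per arm in the FAS:

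P(declare non-inferiority) = Φ[(p_S − p_L + 0.10)/SE − 1.96], SE = √{[p_S(1−p_S) + p_L(1−p_L)]/120}.

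At the margin (SHHS 77%, LHQW 87%) SE = 0.0492 and the result is 2.5%. At the planned rates (90%, 87%) it is 88.5%.

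All withdrawal shares and last-record rates below are assumptions. The article gives only 20% total dropout, which includes consent withdrawal and loss to follow-up.

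**3. Unequal withdrawal, true rates at the margin.** Suppose every withdrawn patient is unrecovered on day 7 and a share s was symptom-free at the last record. LOCF then adds (withdrawn share × s) to each arm's rate. Example, 5% vs 2.5% withdrawn, s = 0.5: p_S = 0.77 + 0.025 = 0.795; p_L = 0.87 + 0.0125 = 0.8825; SE = 0.0471; Φ(0.0125/0.0471 − 1.96) = 4.5%.

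| Withdrawn SHHS vs LHQW | s = 0 | s = 5-10% | s = 25-50% |
|---|---|---|---|
| 3% vs 1.5% | 2.5% | 2.6-2.7% | 3.0-3.6% |
| 5% vs 2.5% | 2.5% | 2.7-2.8% | 3.4-4.5% |
| 5% vs 5% | 2.5% | 2.5% | 2.5% |

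With more withdrawal on LHQW (5% vs 10%) and s = 25-50%, the figure falls to 1.3-0.6%. Exact binomial enumeration of the same rule gives slightly higher values (2.7% at the margin; 3.3% and 3.9% for 3% vs 1.5% with s = 25% and 50%).

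**4. Equal withdrawal, true rates at the margin.** Now let withdrawn patients truly recover at their arm's rate (77% or 87%) while one common rate q is carried forward in both arms. The difference shrinks to −10 × (1 − w) points. With w = 5% it is −9.5 points and false non-inferiority is 3.1%; with w = 10% it is −9.0 points and 3.7-3.8%, for q from 0 to 50%. An imbalance in withdrawal is therefore not required.

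**5. The opposite error, planned rates.** If all withdrawn patients are symptomatic at the last record and half recover by day 7, each arm loses half its withdrawn share.

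- 3% vs 1.5%: 0.885 vs 0.8625, power 82%.
- 5% vs 2.5%: 0.875 vs 0.8575, power 76%.
- 1.5% vs 3% (reversed): 0.8925 vs 0.855, power 89%.

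**6. Null case.** If last-record status equals true day-7 status, the FAS rates do not change and there is no bias.

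No severe-conversion rate is given, so no figure is offered for that outcome.

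**The case against.** The strongest reply is that this rests on silence in a condensed article. Nothing forbids later assessment; Interventions measures stops the intervention, not the visits; Table 1 lists assessments in rows separate from drug administration; and LOCF applies only to values that are missing, so an observed day-7 status would be used. This has force, and it limits the point to what the withdrawal rule permits. It does not remove the point: the article does state that safety grounds take the patient out of the study, and it states what then fills the gap.

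Three stronger readings are tempting and not supported.

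- **Any adverse event forces withdrawal.** The list gives principles for an investigator's decision. The adverse-event item is loosely worded and, beside its neighbours, most plausibly means events that make continuation unsuitable.
- **The last-record sentence governs investigator withdrawals.** It closes the paragraph on patient-initiated withdrawal and loss to follow-up. The link for investigator withdrawals runs through the general LOCF rule.
- **The plan favours SHHS.** The figures in step 3 need more withdrawal on SHHS and relapse of everyone who was symptom-free at the last record. With 5-10% symptom-free the change is 0.1 to 0.3 points, and reversing the imbalance makes the test conservative.

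It is also fair that unblinded investigators are inherent in an open-label trial, and that power in the mildest case (82%) stays above the planned 80%.

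**Conclusion.** The point holds in a limited form. The withdrawal rule lets the investigator take a patient out of the study for safety reasons, no rule keeps that patient under the assessments already scheduled, and LOCF then fills the gap regardless of reason. Obtainable day-7 symptom status and later severe conversion may be replaced by an earlier record for outcome-related reasons.

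Size and direction cannot be determined from the article. Against a nominal 2.5%, false non-inferiority is roughly 2.6-4.5% under assumed withdrawal of 3-5% on SHHS and half that on LHQW with 5-50% symptom-free at the last record, and about 3.1-3.8% under equal 5-10% withdrawal on the step 4 assumptions. It can also be unchanged or lower.

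No claim is made for the per-protocol set (PPS). It should be fixed because the remedy is cheap and brings the FAS closer to its intention-to-treat label, not because a large bias has been shown. Confidence is medium.

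**What to change.** - **Withdrawal criteria and Interventions measures:** state that a new disease, an adverse event that makes continuation unsuitable, or feared harm stops study drug only. Symptoms, disease classification, concomitant drugs and adverse events continue on the Table 1 schedule to day 8, by telephone after discharge, unless consent is withdrawn or contact is lost.
- **Primary outcome and severe conversion:** use the observed day-7 status in the FAS; count severe disease or death by day 7 as not recovered and as a severe-conversion event.
- **Imputation of missing data:** limit LOCF to outcomes that cannot be obtained.

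The cost is a wording change, one eCRF field for the date and reason of stopping drug, and a few telephone contacts. No new visit is needed. Early drug stoppers may still leave the PPS, since "extremely lower compliance will be considered to be excluded from PPS".

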### Sample size

The study hypothesis is SHHS group will be non-inferior to LHQW group. Clinicians and statisticians set the non-inferiority threshold at 10% and predicted that the recovery rate of clinical symptoms after 7 days of LHQW is about 87% and that of SHHS is 90% according to the literature reports on similar drugs. It is estimated that 94 patients for each group, ie. a total of 188 patients are needed to achieve the power of 80% at a one-sided statistically significant level of 0.025. Considering the possible dropout rate of 20%, 240 patients will be enrolled, that is 120 patients for each group.

### Randomization and allocation

A permuted block randomization procedure will be used to allocate 240 eligible patients in a 1:1 ratio. Randomization numbers will be generated using the PROC PLAN process statement in the SAS statistical software package (version 9.4; SAS Inc., Cary, NC, USA). Patients will be assigned to either the SHHS or LHQW group. The Department of Statistics at the Nanjing Medical University will be responsible for randomization. Randomization code will be concealed in opaque envelopes and the allocation information will not be known before randomization procedure.

### Interventions measures

Patients in the SHHS group will receive SHHS granules (10 g per bag), two bags at a time, three times a day, to be swallowed with warm water. The administration of LHQW granules (10 g per bag) will be the same as the SHHS group. The medication course was 7 days (the medication could be stopped in advance if the discharge standard was reached). It will be forbidden to receive other TCM for COVID-19 treatment during the treatment period, including TCM decoctions, granules, or proprietary Chinese medicine. The types, dosage, and cumulative time (including the start and end dates) of the combined therapy drugs should be recorded during the observation period. The intervention will be stopped if there are any severe adverse effects or withdrawal.

### Blinding

The SHHS used in this study is provided by Jiangsu Kanion Pharmaceutical Co. Ltd. (Lianyungang City, Jiangsu Province, China). LianHuaQingWen granules were purchased from Shijiazhuang Yiling Pharmaceutical Co., Ltd. (Shijiazhuang, China). All medications are administered under good manufacturing practices. Even though the trial is open-label, the research assistants who allocate patients to groups will be unaware of their treatment allocation before grouping. Also, assessors and statisticians will be blinded to the group assignment when assessing the efficacy and analyzing the data. Before the analysis and evaluation, all samples and data are anonymized.

### Adherence to study protocol

Protocol adherence during the treatment period will be assessed at each visit and will be based on medication adherence. Frequency distributions are used to describe the proportion of patients in both groups. Medication adherence in the two groups will be calculated and compared according to the ratio of the actual drug administered to the recommended dose. The drugs distributed to the patients and those not administered are documented every day.

## Outcome measures

### Baseline measures for eligibility

During the treatment period, CRFs will be completed with information about the demographic and clinical characteristics of the patients, including age, sex, height, weight, and medical and treatment histories.

### Primary outcomes

The primary outcome is the rate of recovery from four types of patients' self-reported clinical symptoms, including fever, coughing, sore throat and fatigue. It specifically refers to the proportion of patients who met the criteria at the baseline for specific clinical symptoms and achieved recovery at the end of treatment on the seventh day.

### Secondary outcomes

The secondary outcomes are the recovery time of patients self-reported clinical symptoms, SARS-CoV-2 nucleic acid testing negative conversion time, and negative conversion rate, hospitalization time, antipyretic time, the incidence of severe patients, single symptom disappearance time, and disappearance rate.

Criteria for judging the curative effect:(1) Recovery time and cure rate of clinical symptoms: The recovery of clinical symptoms refers to the disappearance of the main symptoms, ie. fever, coughing, sore throat, and fatigue. The cure rate is defined as the proportion of patients whose clinical symptoms recovered after the end of treatment on the seventh day.(2) SARS-CoV-2 nucleic acid testing negative conversion time and negative conversion rate: Taking the first time of the two consecutive respiratory tract SARS-CoV-2 PCR negative tests (sampling interval at least 1 d) as the SARS-CoV-2 PCR testing negative time (the SARS-CoV-2 nucleic acid testing negative conversion time equals the SARS-CoV-2 PCR testing negative time–the diagnosis time of the patient).(3) Hospitalization time: the time from patient admission to discharge. The discharge standard refers to the release from isolation or discharge criterion of the protocol for diagnosing and treating novel coronavirus pneumonia (9th edition).(4) Antipyretic time: The body temperature is less than 37.4°C after treatment, for 24 h or more.(5) The conversion rate of turning to severe patients: the proportion of patients who develop severe infection 7 days after taking medicine.

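### Negative conversion time is counted from diagnosis, so it includes an uncapped pre-randomisation interval that treatment cannot affect

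*Protocol article*

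**What the plan says.** Secondary outcomes, item (2), takes the first of two consecutive negative respiratory PCR samples, at least a day apart, as the end of the interval. It fixes the start in the same sentence: "the SARS-CoV-2 nucleic acid testing negative conversion time equals the SARS-CoV-2 PCR testing negative time", followed by a dash and "the diagnosis time of the patient". The dash is a minus sign, so the clock starts at diagnosis.

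Inclusion criteria require cases "with laboratory confirmed SARS-CoV-2 infection as determined by RT-PCR", so diagnosis comes before allocation. The timing limit given at entry is that "the time of admission is not more than 24 hours". The article gives no limit on time since diagnosis and does not define the diagnosis date further.

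Analysis of secondary outcomes plans Kaplan-Meier medians and a log-rank test for time-to-event data. Table 4 also lays this outcome out as mean, SD and a mean difference with its interval. Table 1 schedules PCR at screening and daily on days 1 to 8.

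**The concern.** A time-to-event comparison in a randomised trial should start when the arms begin to differ. Here the interval has two parts: diagnosis to randomisation, and randomisation to conversion. Only the second can respond to SHHS or LHQW. The first is event-free by selection, because a patient joins as a confirmed case.

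Three consequences follow for this outcome:

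- Patients are counted as at risk for days before they were in the trial, unless delayed entry is handled. The administrative censoring time also varies, because PCR stops at day 8 after a lag that differs between patients.
- Reported times in both arms are longer by roughly the typical lag.
- If the arms differ by chance in mean lag, that difference goes straight into the estimate.

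The choice also differs from the article's other efficacy definitions. The primary outcome is read on day 7 of treatment, antipyretic time refers to temperature after treatment, and conversion to severe disease is judged 7 days after taking the medicine.

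**Working it through.** **The plan's own figure.** The article gives no calculation for negative conversion time. The primary-outcome sample size reproduces closely: (0.87×0.13 + 0.90×0.10) × (1.960 + 0.842)² / 0.13² = 94.3 per group, which rounds up to 95 against 94 stated. With 20% dropout, 188/0.8 = 235, and 240 are planned. The time origin does not enter this calculation, so N is untouched.

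**Assumed inputs, not in the documents.** Post-randomisation conversion SD 3 days; lag SD L of 1 or 2 days. From the documents: 120 per arm.

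**Variance if lag and later conversion are independent.** The ratio of diagnosis-based to randomisation-based variance is 1 + (L/3)².

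- L = 1: 1 + 1/9 = 1.11, a rise of 11%; effective sample 1/1.11 = 0.90.
- L = 2: 1 + 4/9 = 1.44, a rise of 44%; effective sample 1/1.44 = 0.69.

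**Variance with correlation ρ.** The diagnosis-based variance is L² + 9 + 6ρL, against 9 from randomisation.

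- L = 1: 10 + 6ρ, which falls below 9 when ρ < −1/6.
- L = 2: 13 + 12ρ, which falls below 9 when ρ < −1/3.

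A patient enrolled later after diagnosis may well have less time left to conversion, so a negative ρ is plausible and the sign of the precision effect is not known.

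**Chance imbalance.** The difference in mean lag between arms has SD L × √(2/120) = 0.129L: about 0.13 days for L = 1 and 0.26 days for L = 2. Under independence this is the same extra variance as above, seen within a single trial, and not a further loss.

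**Power for a mean difference** (assumed true difference 1.1 days, two-sided 0.05, independence):

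| Lag SD (days) | Total SD (days) | Power |
|---|---|---|
| 0 (from randomisation) | 3.00 | 81% |
| 1 | 3.16 | 77% |
| 2 | 3.61 | 66% |
| 3 | 4.24 | 52% |

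**Log-rank simulation** (assumed Weibull conversion time, shape 2 and scale 6 days, hazard ratio 1.5, censoring at day 8, whole-day lags independent of outcome and arm, 1,000 runs per setting). From randomisation, power was about 83% to 85%. From diagnosis it was 80%, 67% and 55% with lags uniform on 0–2, 0–6 and 0–10 days. With hazard ratio 1, the rejection rate from diagnosis was 4.5% to 5.9%. The Monte Carlo standard error near 5% is √(0.05×0.95/1000) = 0.7 percentage points, so these rates are compatible with 5%. Negative correlation was not simulated.

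**The case against.** The strongest reply is that the lag may be small. Table 1 puts the diagnosis record and a PCR at day −1 and allocation at day −1 to 0. If the diagnosis date means that screening record, the lag is about a day and the effect slight. This stands as a possibility, but the article does not say so, and a patient diagnosed before admission meets the criteria.

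Time from diagnosis, labelled as such, is also a legitimate quantity with a correct median. That stands too: it describes the illness, but it does not isolate the period in which treatment could act. The variance figures describe uncensored means, rest on assumed SDs and independence, and should not be cited as a result for this trial. A fuller analysis plan may handle delayed entry; what is criticised here is the origin that the article states.

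Three stronger readings are tempting and not supported:

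- A reader might infer that the added noise favours a finding of no worse. The 10% margin belongs to the day-7 recovery rate, and no margin is set for this time outcome. Noise unrelated to arm widens a confidence interval, which makes an interval-based non-inferiority claim harder. Harm would need a non-significant log-rank result to be read as similarity, which the article does not plan.
- A reader might infer systematic bias between arms. Randomisation balances the lag in expectation, and the simulated type I error stays near 5%.
- A reader might extend the point to hospital stay, defined as "the time from patient admission to discharge". That is the ordinary meaning of the term, and its pre-entry part is limited by the 24-hour admission criterion.

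**Conclusion.** The point holds for one secondary outcome. The stated origin puts an uncapped interval, untouched by treatment, into negative conversion time, and the planned Kaplan-Meier and log-rank methods, used without delayed entry, treat that interval as time at risk. Reported times are longer by about the typical lag, and a chance imbalance in the lag shifts the estimate. This is not systematic bias.

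The size cannot be fixed from the documents. Under independence, with lag SD 1 to 2 days and conversion SD 3 days, variance rises about 11% to 44%. A sufficiently negative correlation reverses the sign, and a lag confined to about a day makes the matter small. The primary analysis and N = 240 are unaffected, as is the negative conversion rate, whose calculation does not need the diagnosis date.

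**What to change.** Define negative conversion time as the date of the first of the two consecutive negative samples minus the date of randomisation. First dose is an acceptable alternative if applied identically in both arms.

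State what counts as the diagnosis date, record days from diagnosis to randomisation, show it in the baseline table, and use it as a baseline covariate. ANCOVA, already named in the article, can take it on the mean scale; for the time-to-event analysis, a Cox model or a log-rank test stratified by lag can. The covariate keeps whatever prognostic information the lag holds, which also covers the case of negative correlation. Time from diagnosis may stay as a descriptive item.

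The cost is one changed definition and one derived variable. Table 1 already schedules the diagnosis record, allocation and daily PCR, so the dates should be available. No extra patients or visits are needed, and the change can be made before database lock.
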